## Abstract

**Background:**

Nomophobia is a specific phobia characterized by the appearance of anxiety, nervousness, discomfort and distress when the mobile phone is not used and is considered an emerging public health problem because of the negative consequences on the physical and mental health of young people and adolescents, especially women. Neurofeedback-Assisted Mindfulness Training Programs may prove beneficials for improving self-control abilities, a key ability in addressing addictive behaviors. The main objective of this study is to evaluate the impact, in a young population aged 18–35 years, of an intervention based on Neurofeedback-Assisted Mindfulness Training Program (NAMTP) on disorders associated with problematic use of mobile phones. The effect of the intervention on the total score in the nomophobia test and habits of internet and social network use, as well as on signs of depression, anxiety and stress will be analyzed. As a secondary objective, the effect of the intervention on signs of insomnia will be analyzed.

**Methods and design:**

Randomized, controlled clinical-trial with two-parallel groups. 40 young adults (18–35 years) will be included and randomly assigned to Intervention Group-NAMTP or Control Group (CG). The NAMTP will include a total of 25 sessions (2-3/week) during 3-months. Each session will have a duration of 10/15 min. The instrument to be used for the neurofeedback sessions is MUSE^®^ (InteraXon Inc.). Study variables will be collected at the baseline visit and at the final visit (3-months after randomization). During these visits, questionnaires will be administered to evaluate the main and secondary variables that will include the Smartphone Addiction Scale-Short Version, Nomophobia Questionnaire, Depression, Anxiety and Stress Scale 21-item (DASS-21) and Athens Insomnia Scale.

**Discussion:**

This trial will make an important contribution to the need for evidence of effective education programs and other primary care interventions through new non-invasive interventions in reducing the risk of developing addictions to new technologies and alleviating the symptoms of discomfort associated with this problem.

**Ethics and dissemination:**

The project was approved by the Clinical Research Ethics Committee of the Salamanca Health Area (CEIm Code: PI 2023 071340).

**Clinical trial registration:**

ClinicalTrials.gov, http://www.Clinicaltrials.gov/ct2/show/NCT06188910.

## Introduction

### Problematic use of new technologies and their implications for the health of young people and adolescents

Excessive use of new technologies, including mobile phones and uninterrupted connection to the Internet, has been linked in young people to anxiety disorders, depression, attention deficit hyperactivity disorder (ADHD), personality disorders and stress, as well as to sleep problems, substance abuse, unbalanced diets, social isolation and poorer academic performance (1–3).

The excessive and problematic use of the Internet is related to syndromes such as Fear of missing out (FOMO), which is defined as the need to be continuously connected due to the “fear of missing out on something” or nomophobia which comes from the abbreviation of the English term Nomophobia (No MObile PHone PhoBIA) refers to the worry or fear that individuals experience when they are without their mobile phone or they are unable to use it. It is a specific phobia characterized by the appearance of anxiety, nervousness, discomfort and distress when the mobile phone is not used. In addition, it may precede other disorders such as depression or substance abuse (4–6).

The most susceptible and vulnerable population to suffer from nomophobia are young people and adolescents, especially women (4, 7). In addition, in the wake of the COVID-19 pandemic and lockdown, exposure to screens and use of the Internet as a means of escape and socialization has increased (8). Cases have increased to the point that excessive use of mobile phones is being considered an emerging public health problem because of the negative consequences on the physical and mental health of young people (4).

When analyzing possible factors by gender, some studies have concluded that, in women, depression has a stronger relationship with mobile phone addiction (9). The pattern of use could be behind these differences. Several studies reach similar conclusions: men use mobile phones more for leisure and entertainment (online games and video and music media applications), while women use them more for communication and socializing (social networks and applications for chatting and messaging) (7, 9).

However, lower impulse control and psychosocial and demographic factors are identified as major risk factors for nomophobia (4).

### Interventions to treat nomophobia based on neurofeedback-assisted mindfulness training programs

Currently, more and more studies are evaluating the effectiveness of different psychological, pharmacological and healthy lifestyle interventions to treat addiction to new communication technologies and the symptoms associated with their problematic use. A recent meta-analysis evaluated the effectiveness of different interventions including Cognitive-Behavioral Therapy, physical activity, pharmacological treatments or group therapy, among others. The result of this meta-analysis was that all the interventions included in the study decreased Internet addiction to a greater or lesser extent (10).

Neurofeedback (NF) is a form of biofeedback training that uses the recording of brain activity through imaging techniques to achieve, through a process of feedback, the control and regulation of brain activity patterns. Based on the principles of operant conditioning, patients learn gradually through positive reinforcement provided by feedback. Real-time information of brain activity is provided by imaging techniques such as brain magnetic resonance imaging (MRI), functional near infrared spectroscopy (fNIRs) or electroencephalogram (EEG), the latter being the most employed in NF because of lower cost and easier handling in its use (11). The electroencephalographic biofeedback (BF-EEG) or neurofeedback modality consists of placing electrodes or devices on the individual’s head that record the brain’s electrical activity and transmit it to a device. This activity is analyzed by a computer program that converts the EEG waves into visual, auditory or tactile signals that it sends to the patient so that he/she learns to work in a specific wave range, thus achieving the regulation of brain activity (12).

Recently, there has been increasing scientific interest in the effects of the mindfulness-based training programs to reduce stress, anxiety, depression, as well as in the improvement of sleep quality (13–15). Components common to these mindfulness therapies include focus and control of attention, consciousness of sensations and thoughts, and observation. The most consistent EEG findings associated with mindfulness training may be increased theta and alpha power (16). The study by Chow et al. showed a higher global full-band alpha amplitude in patients undergoing meditation training and in patients undergoing EEG-alpha neurofeedback training. In addition, the first group showed a lower upper alpha band ERD in frontal cortex 200–400 ms post-stimulus in the Stroop task, an effect that correlated with the higher alpha amplitudes demonstrated during the intervention (17). Other study suggested that neurofeedback may mediate the effect of mindfulness meditation (18).

NF is a therapy aimed at the prevention, optimization or rehabilitation of altered states of cortical activity. This technique has been shown to be effective in a variety of conditions including anxiety, depression, attention deficit disorder, post-traumatic stress syndrome (PTSD) and insomnia. It has also been used to improve cognitive performance such as memory and attention (11, 19). NF techniques have been shown to be effective in the treatment of anxiety. In 2017, clinical guidance published by the Canadian Agency for Drugs and Technologies in Health (CADTH) suggested that, compared to receiving no treatment, there was significant improvement when NF is used in patients with PTSD and Generalized Anxiety Disorders (12).

Certain training in mindfulness techniques, focused on focusing attention on the present moment, have been shown to reduce the effects of nomophobia related to problematic mobile phone use (20). Some research has shown that even a single session of mindfulness can alleviate your symptoms (18). Several studies have shown that mindfulness is beneficial for improving self-control abilities, a key ability in addressing addictive behaviors (18, 20), achieving, among other effects, an increase in alpha power (waves related to focus and attention) in the EEG study.

In view of the unstoppable development of new technologies and their increasingly widespread use in our society, there is a need to investigate the health problems derived from their inappropriate use. Interventions based on Neurofeedback-Assisted Mindfulness Training Programs could improve anxiety and other symptoms related to the problematic use of internet and new technologies.

The main objective of this study is to evaluate the impact, in a young population aged 18–35 years, of an intervention based on Neurofeedback-Assisted Mindfulness Training Program on disorders associated with problematic use of mobile phones and internet. The effect of the intervention on the total score in the nomophobia test and habits of internet and social network use, as well as on signs of depression, anxiety and stress will be analyzed. As a secondary objective, the effect of the intervention on sleep quality and signs of insomnia will be analyzed.

## Methods and analysis

### Design

The design of this study corresponds to a clinical trial with two parallel randomized groups.

### Study population

The study participants will be recruited in the consultations of the urban Health Centers of the Salamanca Health Area. Subjects will be included by consecutive sampling taking into account the following selection criteria:

Inclusion criteria: age between 18 and 35 years, having one or more Smartphone-type mobile devices, having a compatible mobile phone to install and use the MUSE^®^: EEG Meditation & Sleep application (the description of this device and its operation is developed later in this manuscript), being fully functional (physically and mentally free of known disorders and disabilities), willing to voluntarily participate in the study and signing the informed consent form.

Exclusion criteria: History of severe psychiatric disorders (such as schizoaffective disorders, bipolar disorder, major depressive episode with symptoms or other non-organic psychotic disorders) requiring psychiatric treatment in the 6 months prior to inclusion in the study, history of brain injury or other problems contraindicating the use of neurofeedback.

### Sample size calculation

The sample size estimation is based on the expected results in one of the main variables, which is the change in anxiety symptoms. This estimate was made using the results collected in the study by Abdian et al. (21), who conducted a study similar to the one we propose using the DASS-21 anxiety scale score as a change variable, obtaining a mean difference between groups after the intervention of 3.9 points in this questionnaire. Accepting an alpha risk of 0.05 and a beta risk of 0.2 in a bilateral contrast, 40 participants (20 participants in the experimental/intervention group and 20 in the control group) are required to detect a clinically relevant difference equal to or greater than 3.9 points on the DASS-21 anxiety questionnaire. The statistical power of a hypothesis test is 93% to detect the difference between the means as statistically significant. The common standard deviation on this questionnaire, according to data provided by Abdian et al. (21) is assumed to be 3.7. A loss to follow-up rate of 30% has been estimated.

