### Inclusion, randomization and procedures

A researcher will contact by telephone to arrange a visit with the selected individuals at the health centers. During this visit, the study will be presented, any doubts will be resolved and the informed consent form will be signed. After verifying that the subject meets the inclusion criteria, a baseline evaluation will be carried out in which clinical and sociodemographic variables and the study change variables will be collected. Finally, each participant will be randomly assigned to one of the 2 groups (Intervention group (IG)- Neurofeedback-Assisted Mindfulness Training Program) or Control Group (CG). Randomization will be performed randomly using the Epidat 4.2 program (22) with a ratio of 1/1. The allocation will be kept hidden until participants are assigned to each group. A final evaluation will be performed on all participants at the end of the study (3 months after randomization) to re-evaluate clinical, sociodemographic and study change variables (Figure 1).

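### The stated 93% power ignores the plan's own 30% loss to follow-up; with that loss, 40 randomised participants give about 77% by the planned t-test

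*Protocol article*

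**What the plan says.** All the planning figures stand in one paragraph of the protocol article, under Sample size calculation.

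- Error rates: "Accepting an alpha risk of 0.05 and a beta risk of 0.2 in a bilateral contrast".
- Size: "40 participants (20 participants in the experimental/intervention group and 20 in the control group) are required".
- Target: "to detect a clinically relevant difference equal to or greater than 3.9 points on the DASS-21 anxiety questionnaire".
- Common standard deviation: it "is assumed to be 3.7", on the basis of a cited study.
- Power: "The statistical power of a hypothesis test is 93% to detect the difference between the means as statistically significant".
- Attrition: "A loss to follow-up rate of 30% has been estimated".

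The paragraph does not say whether the 40 are participants randomised or participants with a final score, nor how the 30% enters the calculation. The Methods and design part of the abstract settles the first question: 40 young adults are to be included and randomly assigned. Inclusion, randomization and procedures gives the allocation, "with a ratio of 1/1". Data analysis names Student's t-test for comparing two independent groups, with the Mann-Whitney test as the non-normal alternative.

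**The concern.** The paragraph sets an accepted beta of 0.2 (80% power), a stated power of 93%, a required size of 40 and a 30% loss side by side, without saying which figure belongs to which situation. If 40 is the number randomised, the 93% can describe the trial only if everyone completes it, and the same paragraph expects that not to happen. A reader who takes 93% as the power of the design will credit the trial with a type II error of about 7% for the DASS-21 anxiety difference on which it was sized. What matters is how much power is left at the attrition the plan itself expects, and whether that still reaches the 80% it set out to accept.

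**Working it through.** **Inputs.** Difference Δ = 3.9, SD σ = 3.7, two-sided α = 0.05, target power 80%, 20 per arm and 30% loss (all from Sample size calculation); 1:1 allocation (Inclusion, randomization and procedures); two-sample t-test (Data analysis). Standardised difference: 3.9/3.7 = 1.054.

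**Formulas.** With n completers per arm, SE = σ√(2/n) and λ = Δ/SE.
- Normal approximation: power ≈ Φ(λ − 1.96).
- t-test: power = P(|T| > t₀.₉₇₅), where T is noncentral t with 2n − 2 degrees of freedom and noncentrality λ.

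**Step 1. The plan's own figure, 20 completers per arm.**
- SE = 3.7 × √(2/20) = 1.170; λ = 3.9/1.170 = 3.333.
- Normal: Φ(3.333 − 1.960) = Φ(1.373) = 91.5%.
- t-test, 38 degrees of freedom: 90.1%.

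The inputs are printed to one decimal. Taking them as favourably as rounding allows (3.95 and 3.65) gives 92.8% (normal) or 91.5% (t). The stated 93% is therefore close to a normal-approximation result for 20 completers per arm and slightly high for the t-test. It is a no-loss figure.

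**Step 2. After the stated loss.**
- Completers per arm: 20 × (1 − 0.30) = 14.
- SE = 3.7 × √(2/14) = 1.398; λ = 3.9/1.398 = 2.789.
- Normal: Φ(2.789 − 1.960) = Φ(0.829) = 79.6%.
- t-test, 26 degrees of freedom: 76.6%.

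| Completers per arm | t-test | Normal approximation |
|---|---|---|
| 20 (no loss) | 90.1% | 91.5% |
| 14 (30% loss) | 76.6% | 79.6% |

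**Step 3. Sensitivity to rounding at 14 per arm.** With (3.85, 3.75) and then (3.95, 3.65), the t-test gives 74.4% to 78.7% and the normal approximation 77.5% to 81.7%. The t-test stays below 80% throughout; the normal approximation falls on either side of it.

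**Step 4. Completers needed for 80%.** Normal: n = 2(1.960 + 0.842)² × (3.7/3.9)² = 14.13, so 15 per arm. The t-test needs 16 (82.2%, against 79.6% at 15). Allowing for 30% loss, 15/0.7 = 21.4, so 22 per arm; 16/0.7 = 22.9, so 23 per arm. That is 44 to 46 randomised, against 40.

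**The case against.** **The figures may describe two scenarios.** The paragraph can be read as 80% power after losses and about 93% if all 20 per arm complete. On that reading beta 0.2 and 93% do not contradict each other, and nothing in the text claims 93% after loss. This is fair, and it is why the point is not put as a contradiction. But the text does not attach the 93% to full follow-up, and the only attrition it expects is 30%.

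**A reader might infer that the 93% is an arithmetical error.** The documents do not support that. The formula is not named, the inputs are rounded, and 91.5% (92.8% with favourable rounding) is near enough that method and rounding could account for the difference.

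**A reader might also infer that 20 per arm came from multiplying 15 by 1.3** (19.5) instead of dividing by 0.7. The match is suggestive, but the protocol does not say how the 30% was used, and the shortfall does not depend on the cause.

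**The miss against 80% is small.** By normal approximation it is 0.4 points and can vanish within input rounding. That stands. It is firm only for the t-test, which is the test the plan names.

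**Intention-to-treat keeps all 40.** Data analysis does commit to analysing everyone who enters. Keeping a participant in the analysis set does not by itself recover a final score that was never observed.

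**Conclusion.** The point holds in a limited form. The 93% is a slightly optimistic figure for full follow-up (90.1% by t-test, 91.5% by normal approximation) and is not the power of the design at its own expected attrition. With 30% lost, power is about 77% by the planned t-test, some 16 points below the stated figure and 3.4 points below the 80% implied by beta 0.2. By normal approximation it is 79.6%, which is at the target for practical purposes.

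This rests on 40 being the number randomised, as the abstract states; on analysis of observed final scores; and on equal loss in the two arms. For 28 completers in all, an equal split is the most favourable case, because 1/n₁ + 1/n₂ is then smallest.

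It would go too far to conclude that the trial is seriously underpowered, or that its type II error is three times what it claims: that ratio compares a 30%-loss scenario with a figure that plausibly assumes none. The consequence is one of reporting. The only power statement in the article overstates what a non-significant anxiety result could exclude.

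**What to change.** In Sample size calculation, replace the 93% sentence with:

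> 40 randomised; power is about 90% (two-sample t-test) if nobody is lost and about 77% with the expected 30% loss (14 per arm), for 3.9 points, SD 3.7, two-sided 0.05.

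This also makes clear that 40 is the number randomised and how the 30% enters. The change is wording only: the sample size, endpoint and analysis stay as they are. The cost is that the stated power becomes less favourable and that the plan acknowledges falling a little short of 80% by the t-test at its expected attrition.

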### Inclusion, randomization and procedures

A researcher will contact by telephone to arrange a visit with the selected individuals at the health centers. During this visit, the study will be presented, any doubts will be resolved and the informed consent form will be signed. After verifying that the subject meets the inclusion criteria, a baseline evaluation will be carried out in which clinical and sociodemographic variables and the study change variables will be collected. Finally, each participant will be randomly assigned to one of the 2 groups (Intervention group (IG)- Neurofeedback-Assisted Mindfulness Training Program) or Control Group (CG). Randomization will be performed randomly using the Epidat 4.2 program (22) with a ratio of 1/1. The allocation will be kept hidden until participants are assigned to each group. A final evaluation will be performed on all participants at the end of the study (3 months after randomization) to re-evaluate clinical, sociodemographic and study change variables (Figure 1).

**Figure 1 fig1:**
[figure not shown]
Flow-chart diagram of the study.

The study, evaluations and intervention will be carried out at the University Hospital of Salamanca and the Institute of Biomedical Research of Salamanca (IBSAL). The recruitment of participants will be carried out in the primary care clinics of the Salamanca Health Area, Spain.

### Study variables

Study variables will be collected at the baseline visit and at the final visit (3 months after randomization).

Primary outcomes:

Smartphone addiction: The short version of the Smartphone Addiction Scale (SAS-SV), validated in Spanish by Lopez-Fernandez (23), will be used. This scale consists of 10 items and scores higher than 31 are considered susceptible to the presence of addiction to mobile phones (23). In addition, the age at the beginning of the use of new technologies, age of the first mobile phone, type of devices used to connect to the Internet, hours of daily use of the mobile phone, most frequent activities carried out with the mobile phone (calls and messages, games, entertainment, social networks, Internet search, etc.) will also be collected.Nomophobia: The Nomophobia Questionnaire (NMP-Q) will be used for its evaluation. It is a questionnaire composed of 20 items and validated in Spanish by González-Cabrera (24). The range of scores varies from 20 to 140 points. Scores above 20 would indicate the presence of nomophobia (24).Depression, anxiety and stress: The Spanish version of the Depression, Anxiety and Stress Scale 21-item (DASS-21) was used to assess the presence of negative emotional states (25). This questionnaire consists of 21 items divided into three subscales or categories of 7 items each: depression, anxiety and stress. Each item is scored according to the presence of symptoms during the last week on a four-point Likert scale. The final score is obtained with the sum of the scores for each subscale. The DASS-21 has been used to assess nonclinical samples in different age ranges, including adolescence (26). The presence of adverse mental health symptoms was considered according to the cut-off points proposed by Roman et al. (27) in the validation study with a sample of young people in Spain: DASS-21-Depression≥6 points, DASS-21-Anxiety≥6 points, and DASS-21-Stress≥5 points.

Secondary outcomes:

Sleep quality and signs of insomnia: It will be evaluated through the Athens Insomnia Scale (AIS). This is a tool that helps in the diagnosis and assessment of insomnia according to ICD-10 diagnostic criteria. It consists of 8 items, with four response options scoring from 0 to 3. A higher score on the scale indicates the presence of insomnia symptoms (28).

Other variables:

In the baseline evaluation, age, sex, educational level, and employment status will be collected. The level of physical activity will be asked by administering the International Physical Activity Questionnaire (IPAQ). For this purpose, the short 7-item version validated in Spanish will be used. This questionnaire evaluates the intensity, frequency and duration of physical exercise performed in the last 7 days. It allows us to classify the level of activity as high, moderate or low (29).

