### Data analysis

Variables will be collected in a database in the SPSS v.28 statistical package. An intention-to-treat analysis will be performed, so that the results of all individuals entering the study will be analyzed, regardless of whether or not they complete the study protocol. This will allow us to assess the effect according to the percentage of adherence to the sessions, as well as to avoid biased calculations by including all participants. The normality of the variables collected will be evaluated using the Kolmogorov–Smirnov test (34). The characteristics of the sample will be expressed by frequency distribution and percentages for categorical variables; and calculation of mean and standard deviation for quantitative variables. In the case of parametric distributions, the association between variables will be analyzed with Student’s *t*-test and analysis of variance (ANOVA). In the case of not following a normal distribution, the corresponding nonparametric tests of the previously mentioned tests will be used. The Student’s *t*-test (Mann Whitney U) for independent samples will be used to compare the means between two groups, evaluating the change within the same group with the Student’s *t*-test for paired data (Wilcoxon test). The relationship between quantitative variables will be analyzed using Pearson’s correlation coefficient or Spearman’s correlation coefficient for non-normal variables. A repeated measures analysis (a between-groups repeated measures ANOVA) will be performed as well as an estimation of the parameters and the effect size. For the bilateral contrasts of hypotheses an alpha risk of 0.05 is set as the limit of statistical significance.

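### The NMP-Q presence rule sits at the floor of the scale, so a present/absent reading of nomophobia would carry almost no information; the total-score comparison is unaffected

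*Protocol article*

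**What the plan says.** In Study variables, nomophobia measured by the NMP-Q is one of the listed primary outcomes. On the instrument the article says "It is a questionnaire composed of 20 items", and then "The range of scores varies from 20 to 140 points. Scores above 20 would indicate the presence of nomophobia". It gives no other NMP-Q cut-off or severity band.

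The Background of the abstract states how the outcome is to be used: "The effect of the intervention on the total score in the nomophobia test" is what will be analysed. The end of the Introduction repeats this.

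Data analysis plans a t-test or Mann-Whitney test "for independent samples will be used to compare the means between two groups", together with paired tests, correlations and a repeated measures ANOVA. It also says that sample characteristics will be given by "frequency distribution and percentages for categorical variables". It names no test of NMP-Q case status.

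The criteria in Study population include no NMP-Q threshold.

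**The concern.** A presence rule should separate people with a condition from people without it. Here the threshold and the scale minimum are the same number, in adjacent sentences. One item answered one step above the lowest option is enough to make a participant a case.

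The label is likely to be used. Study variables also gives presence cut-offs for the other two primary instruments: SAS-SV above 31, and DASS-21 subscales at 6, 6 and 5 or more. A table of the number with each condition, by arm and visit, is therefore a foreseeable product.

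For nomophobia, that table would show nearly everyone affected, before and after, in both arms. A reader could take this as a very high prevalence among young adults attending health centres, or as evidence that the programme did not resolve nomophobia. Both readings would come from the rule and not from the participants.

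**Working it through.** **Inputs.** From Study variables: 20 items, range 20 to 140, case if the total exceeds 20. From Sample size calculation: 20 participants per arm.

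**Step 1: reproduce the stated range.** The article does not give the item scoring. A score of 1 to 7 per item fits the range: 20 × 1 = 20 and 20 × 7 = 140. A total of 20 then requires the lowest answer to every item.

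**Step 2: what the rule labels.**
- Possible totals: 140 − 20 + 1 = 121.
- Totals labelled as nomophobia: 21 to 140, which is 120. 120/121 = 99.2%.
- Response patterns labelled as no nomophobia: 1 of 7^20, about 1 in 8.0 × 10^16.

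These counts describe the rule. They are not a forecast of prevalence.

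**Step 3: share of non-cases (assumption).** The article gives no NMP-Q distribution. Suppose each item is at its minimum with probability q, independently. Then P(total = 20) = q^20. On average 20(1 − q) items lie above the minimum, each adding 1 to 6 points, which bounds the mean total.

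| q | Non-cases | Cases | Mean total lies between |
|---|---|---|---|
| 0.5 | 0.0001% | over 99.9% | 30 and 80 |
| 0.8 | 1.2% | 98.8% | 24 and 44 |
| 0.9 | 12.2% | 87.8% | 22 and 32 |
| 0.95 | 35.8% | 64.2% | 21 and 26 |

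Positive correlation between items would raise the non-case share above q^20, with q itself as the upper limit. The case share therefore falls clearly below 100% only when many participants give the lowest answer to essentially the whole questionnaire.

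**Step 4: what a case comparison could detect (illustration; no such test is planned).** Take 20 per arm, complete follow-up, and all 20 controls as cases. The two-sided Fisher p-value when k intervention participants score exactly 20 is 2 × C(20,k)/C(40,k).
- k = 4: 2 × 4,845/91,390 = 0.106.
- k = 5: 2 × 15,504/658,008 = 0.047.

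At least 5 of 20 intervention participants would have to reach the exact floor. Exact power is 0.3% if the true proportion reaching it is 5%, 4.3% if it is 10%, and 37% if it is 20%.

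**Step 5: change within a person.** A fall from 140 to 21 covers 119 of the 120 points of the range and leaves the participant a case.

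**The case against.** The strongest reply is that nothing in the plan depends on the cut-off. The objective names the total score. The tests in Data analysis are for quantitative variables. The cut-off is not an entry criterion and does not enter the sample size. The sentence on frequencies and percentages concerns description of the sample, not comparison of outcomes. The presence statement cites a validation study and may only describe the instrument, perhaps compressing a graded description in that source.

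Much of this stands. A reader might infer that nomophobia as a primary outcome cannot show an effect. The documents do not support that: the comparison of mean totals never passes through the cut-off, and its estimate and power are untouched. Nor is it literally impossible for the label to change, since a total of exactly 20 can occur. The Fisher figures above describe a test that the article does not plan.

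The reply does not rescue the sentence itself. It is a stated presence rule inside a primary outcome definition, and on the article's own range it cannot discriminate. If it will not be used, it has no place there. If it is used, even only to describe the sample, the result is uninformative. What the cited validation study says cannot be settled from the article, so no replacement cut-off is offered here.

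**Conclusion.** The point holds for the present/absent label and for any prevalence or responder reading of it. It does not hold for the nomophobia outcome as a whole.

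That the threshold equals the scale minimum follows from the stated range alone. The expectation of near 100% cases in both arms at both visits rests on one assumption: that few participants, in a sample not selected for nomophobia, give the lowest answer to all 20 items. Under the independence model the case share is 98.8% or more for q up to 0.8. It drops to 87.8% at q = 0.9 and 64.2% at q = 0.95, where mean totals lie close to the floor.

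The sentence should be corrected, but the main inference is not at risk.

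**What to change.** In Study variables, delete the presence rule for NMP-Q, or check it against the cited Spanish validation study and correct it. Do this before any data are analysed, so that no cut-off is chosen with results in view.

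In Study variables and Data analysis, state that NMP-Q is analysed and reported as the total score (20 to 140), compared between arms at 3 months with the baseline total as covariate. Data analysis does not now name that adjustment, but the baseline total is already collected.

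Do not report a nomophobia prevalence or responder rate based on scores above 20.

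The cost is a few sentences. There are no new data, no change to sample size, and no loss against the stated objective, which already names the total score.
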